## Abstract

**Background:**

Chronic obstructive pulmonary disease (COPD) is a common chronic respiratory disease. The occurrence of COPD is associated with gut microbiota, meticulous metabolism and inflammation. Acupuncture may be effective as an adjunctive therapy for COPD, but the available evidence is limited. This study aims to confirm whether acupuncture therapy has an adjunctive therapeutic effect on COPD and to investigate the relationship between the efficacy and the gut microbiota, metabolomics and inflammation.

**Methods:**

This study is a multicenter randomized controlled trial. A total of 72 patients with stable COPD eligible will be randomized in a 1:1 ratio to receive either manual acupuncture (MA) or sham acupuncture (SA) without puncturing the skin. There will be no changes to the essential medicines used for all patients. The intervention will be 12 weeks, 3 times per week and follow-up will be 52 weeks. The primary outcome will be the change in COPD Assessment Test (CAT) score before and after treatment. Secondary outcomes will include modified Medical Research Council (mMRC), St. George’s Respiratory Questionnaire (SGRQ), 6-min walk test (6MWT), and the number of moderate or severe acute exacerbations during follow-up. A total of 36 healthy volunteers will also be recruited as normal control. In addition, feces and blood will be collected from each participant to characterize the gut microbiota, metabolomics, immune cells and inflammatory cytokines. Differences between COPD patients and healthy participants will be observed, as well as changes before and after treatment in MA and SA groups. Ultimately, the correlation among gut microbiota, metabolomics, immune cells, inflammatory cytokines and clinical efficacy in COPD patients will be analyzed.

**Discussion:**

This study will evaluate the efficacy and provide preliminary possible mechanisms of acupuncture as an adjunctive therapy in treating COPD. In addition, it will identify biomarkers of the gut microbiota, metabolites, immune cells, and inflammatory cytokines associated with therapeutic efficacy. The results of this study will be published in a peer-reviewed journal.

## 1 Introduction

Chronic obstructive pulmonary disease (COPD) is mainly characterized by airway obstruction and airflow limitation, and the main clinically manifestations include chronic cough, sputum and shortness of breath after activity, leading to a serious decline in the life quality and working ability of patients (1, 2). There are more than 300 million COPD patients in the world, and about 99.9 million in China (3). COPD has become the third leading cause of death in the world after ischemic heart disease and stroke, with more than 3 million deaths annually (4, 5). It is estimated that by 2060, the number of deaths from COPD and related diseases will exceed 5.4 million per year (6). The burden of disease caused by COPD is the fifth highest in the world, with per capita direct medical costs in China ranging from 72 to 3,565 dollars per year, accounting for 33.33 to 118.09% of annual per capita income (7, 8). The bronchodilators, inhale corticosteroids (ICS), mucolytics as well as antibiotics are currently the mainstay of COPD treatment (7), with the advantage of rapid short-term relief of dyspnea (9), but not reversal of the COPD disease process (10, 11). The improvement in clinical outcomes is based on long-term maintenance of the medication, but the patients need to bear the risk of adverse effects such as bacterial resistance (12), lung infections (13), and hearing loss (14). Furthermore, the administration of these drugs is often complicated and difficult for older and less-educated patients to acquire and adhere to (15). The financial burden of high drug prices is also difficult to ignore (16). Therefore, it is imperative to find economical and effective treatments with fewer adverse effects.

Acupuncture, as part of traditional Chinese external medicine, is widely used in the management of various diseases and considered to be one of the ideal complementary alternative therapies for COPD. Existing evidence of randomized controlled trials and systematic reviews suggests that acupuncture is effective in improving dyspnea symptoms, exercise tolerance, quality of life scores, and lung function in COPD patients compared with sham acupuncture (17). Acupuncture-assisted treatment of COPD can effectively improve life quality of patients and is more effective than applying conventional drug therapy alone (18–20). However, there are some shortcomings in the available clinical studies: for example, vague description of research methods, insufficiently reported details of the specific acupuncture/sham acupuncture method setup in the interventions, short follow-up period, and few reports on safety. Moreover, the underlying mechanism of the efficacy of acupuncture remains poorly defined.

The pathogenesis of COPD is closely associated with immune dysfunction and persistent inflammation, in which the immune homeostasis of Th17 cells and Treg cells plays an important role (21, 22). Th17 cells, named after their specific secretion of interleukin 17 (IL-17), mediate immune defense, which recruits and activates neutrophils and promotes the release of inflammatory factors (23). Treg cells mediate immune tolerance and inflammatory suppression, and negatively regulate immune cell activation and proliferation (24). Under normal body function, the two are in dynamic balance to maintain natural immune homeostasis. In pathological conditions, over-activation of Th17 cells and insufficient Treg cells can lead to hypersecretion of airway mucus and persistent inflammation, resulting in worsening of COPD (25).

The gut microbiota and the metabolome are also important in the progression of COPD (26). Studies have shown that the fecal microbiome of COPD patients is different from that of healthy individuals (27). Streptococcus, streptococcus vestibularis, and lachnospiraceae are associated with reduced lung function (28). Human commensal bacteria can ferment dietary fiber into short-chain fatty acids (SCFA), which can activate immune cells via the NLRP3 inflammatory vesicle, affecting lung inflammation and promoting COPD progression (29, 30). Metabolomics analyses have revealed that abnormalities in amino acid metabolism, lipid metabolism, energy production, as well as oxidative and antioxidant abnormalities affect the pathogenesis of COPD (31, 32). Elevated serum levels of lysine, pyruvate, 3-hydroxybutyrate, and glutamine are strongly related to acute exacerbations in patients with COPD (33). Mammalian target of rapamycin (mTOR) is a critical enzyme body that regulates cell proliferation and metabolic processes. It has been found that certain metabolites can activate the mTOR pathway and promote the differentiation of Th17 cells, as well as bind to scaffolding proteins and regulatory proteins to form mTOR complexes, induce the expression of the hypoxia-inducible factor-1α (HIF-1α), and mediate the proteasomal degradation of the forkhead-box protein P3 (FOXP3, the key transcription factor in Treg cells) to inhibit the function of Treg cells (34). Evidence suggests that acupuncture may have a therapeutic effect on COPD by decreasing the levels of tumor necrosis factors-γ (TNF-γ) and IL-4 (35), which are related to the balance of the Th17/Treg pattern. Meanwhile, acupuncture has a certain regulatory effect on gut microbiota and metabolites (36, 37). However, there are no studies linking chronic inflammation, intestinal flora, and metabolomics to investigate the mechanism of acupuncture to improve COPD from a multi-omics perspective.

Therefore, a randomized, parallel-controlled and long-follow-up trial is designed to further validate the clinical efficacy of acupuncture as an adjunctive therapy for patients with COPD and to explore the relationship between clinical efficacy and gut microbiota, metabolome and inflammation.

## 2 Materials and methods

### 2.1 Objectives

This trial aims to:

(1)Evaluate the immediate and long-term efficacy and safety of acupuncture in treating COPD;(2)Investigate whether acupuncture can improve the clinical symptoms of COPD patients by influencing the gut microbiota and metabolome, regulating the dynamic balance of immune cells Th17/Treg and the levels of related inflammatory cytokines.

### 2.2 Trial design and setting

This is a prospective, parallel-controlled, multicenter, randomized controlled trial with blinded participants, outcome assessors, and statistician. A total of 72 COPD patients eligible will be randomly assigned to the manual acupuncture (MA) group and sham acupuncture (SA) group in a 1:1 ratio. The entire study period consists of 1 week of screening, 12 weeks of treatment and 52 weeks of follow-up. Both groups of patients will be assessed on the relevant scales throughout the study cycle (including at the time of enrollment, during the intervention period and the follow-up period), and changes in the clinical symptoms of COPD patients will be observed to clarify the effect of acupuncture on COPD. Furthermore, 36 healthy volunteers will also be recruited as a normal control group and will not receive any treatment. The trial will be conducted in four sub-centers: the Affiliated Hospital of Chengdu University of Traditional Chinese Medicine, the Sichuan Provincial People’s Hospital, the Chengdu Second People’s Hospital, and the Meishan Hospital of Traditional Chinese Medicine.

The study protocol is developed following The Consolidated Standards of Reporting Trials (CONSORT) Framework (38) and The Standards for Reporting Interventions in Clinical Trials of Acupuncture (STRICTA) (39), and will be reported in accordance with the Standard Protocol Items: Recommendations for Interventional Trials (SPIRIT) guidelines and checklist (40). The flow chart of trial procedures is shown in Figure 1, and the study schedule is depicted in Table 1.

**FIGURE 1 F1:**
[figure not shown]
Research flow chart.

**TABLE 1 T1:** Schedule of enrollment, intervention, and assessments.

	Study period							
**Items**	**COPD participants**							**Healthy participants**
	**Enrollment**	**Baseline**	**Intervention phase**			**Follow-up**		**Enrollment**
	**Week -1**	**Week 0**	**Week 4**	**Week 8**	**Week 12**	**Week 38**	**Week 64**	**Week -1**
**Enrolment**								
Eligibility screen	×							×
Informed consent		×						×
Demographic characteristics		×						×
Disease history		×						×
Combined disease		×						×
Medication history		×						×
Randomization		×						
**Intervention**								
Acupuncture group			×	→	×			
Sham acupuncture group			×	→	×			
**Examinations**								
Blood detection		×			×			×
Feces detection		×			×			×
**Assessments**								
CAT		×	×	×	×	×	×	
mMRC		×	×	×	×	×	×	
SGRQ		×	×	×	×	×	×	
6-MWT		×			×	×	×	
Times of AECOPD						×	×	
Blinding assessment					×			
Safety assessment			×	×	×			
Adherence evaluation		×	×	×	×	×	×	

COPD, chronic obstructive pulmonary disease; CAT, COPD Assessment Test; mMRC, modified Medical Research Council; SGRQ, St. George’s Respiratory Questionnaire; 6MWT, 6-min walk test; AECOPD, acute exacerbation of chronic obstructive pulmonary disease.

### 2.3 Participants

#### 2.3.1 Source of participants

Recruitment strategies include posters, respiratory outpatients and previous inpatients. Patients will be informed of study specifics, including study purpose, subgroup status, interventions, treatment period, benefits, and potential risks. Patients interested in participating in this study will be critically judged and admitted by respiratory specialists based on inclusion and exclusion criteria and an informed consent form must be obtained prior to randomization into groups. All participants information will be kept confidential.

#### 2.3.2 Eligibility criteria for patients with COPD

##### 2.3.2.1 Inclusion criteria

Patients who meet the following criteria will be included (Table 2):

**TABLE 2 T2:** Eligibility criteria.

COPD participants
**Inclusion criteria**
Patients who meet the following criteria will be included: (1) Diagnosis of COPD according to the *Global Initiative for Chronic Obstructive Lung Disease (GOLD) 2022 Report*; (2) Age between 40 and 80 years (no gender restrictions); (3) Pulmonary function tests: FEV1 between 25 and 80% after inhaled bronchodilators; (4) At least 1 moderate or severe acute exacerbation within the past year; (5) Stable condition without acute exacerbation in the last 4 weeks; (6) Being under regular medical treatment in accordance with the GOLD recommended dosing regimen within 3 months prior to enrollment, or not yet receiving any treatment; (7) Volunteering to cooperate with the study and sign an informed consent form.
**Exclusion criteria**
Patients who meet any of the following conditions will be excluded: (1) Being with severe cardiovascular, neurological, hematological, immune system, and malignant tumor diseases; (2) Being with other respiratory diseases that have a significant impact on the study (active tuberculosis, bronchial asthma, severe bronchiectasis, primary pulmonary hypertension, interstitial lung disease, etc.); (3) History of segmentectomy, wedge resection, lobectomy, total pneumonectomy, or lung volume reduction (including bronchoscopic lung volume reduction) for COPD; (4) Requiring continuous oxygen therapy according to long-term oxygen therapy (LTOT) criteria (oxygen therapy duration > 15 h/d); (5) Unable to perform pulmonary function tests, walk independently, or cooperate in completing questionnaires; (6) Presence of persistent breakage or infection of skin tissue at the site of needling, coagulation dysfunction, skin allergies; (7) Having participated in other clinical trials or performed acupuncture for respiratory disease within the past 3 months; (8) Application of antibiotics within the past 3 months; (9) Application of systemic glucocorticoids within the past 1 month; (10) Long-term application of probiotics and prebiotics; (11) Suffering from severe gastrointestinal disorders and gut microbiota disorders; (12) Being pregnant or in lactation.
**Healthy participants**
**Inclusion criteria**
Participants who meet the following criteria will be included as normal control: (1) Age between 40 and 80 years (no gender restrictions); (2) Not in sub-healthy state according to the “Clinical Guidelines of Chinese Medicine on Sub-health” of China Association of Chinese Medicine; (3) No diagnosis of respiratory system diseases, digestive system diseases, and other conditions or states of obvious clinical significance within 1 year prior to enrollment; (4) Volunteering to cooperate with the study and sign an informed consent form.
**Exclusion criteria**
Participants who meet any of the following criteria will be excluded from the normal control group: (1) Regular application of probiotics, prebiotics, or antibiotics; (2) Having gastrointestinal symptoms in the last week; (3) Being pregnant or in lactation; (4) Being in other clinical trials.

COPD, chronic obstructive pulmonary disease.

(1)Diagnosis of COPD according to the Global Strategy for the Diagnosis, Management, and Prevention of Chronic Obstructive Lung Disease: the GOLD science committee report 2022 (41);(2)Age between 40 and 80 years (no gender restrictions);(3)Pulmonary function tests: FEV1 between 25 and 80% after inhaled bronchodilators;(4)Stable condition without acute exacerbation in the last 4 weeks;(5)Being under regular medical treatment in accordance with the GOLD recommended dosing regimen within 3 months prior to enrollment, or not yet receiving any treatment;(6)Volunteering to cooperate with the study and sign an informed consent form.

##### 2.3.2.2 Exclusion criteria

Patients who meet any of the following conditions will be excluded:

(1)Being with severe cardiovascular, neurological, hematological, immune system, and malignant tumor diseases;(2)Being with other respiratory diseases that have a significant impact on the study (active tuberculosis, bronchial asthma, severe bronchiectasis, primary pulmonary hypertension, interstitial lung disease, etc.);(3)History of segmentectomy, wedge resection, lobectomy, total pneumonectomy, or lung volume reduction (including bronchoscopic lung volume reduction) for COPD;(4)Requiring continuous oxygen therapy according to long-term oxygen therapy (LTOT) criteria (oxygen therapy duration >15 h/d) (42);(5)Unable to perform pulmonary function tests, walk independently, or cooperate in completing questionnaires;(6)Application of antibiotics within the past 3 months;(7)Application of systemic glucocorticoids within the past 1 month;(8)Long-term application of probiotics and prebiotics;(9)Suffering from severe gastrointestinal disorders and gut microbiota disorders;(10)Presence of persistent breakage or infection of skin tissue at the site of needling, coagulation dysfunction, skin allergies;(11)Having participated in other clinical trials or performed acupuncture for respiratory disease within the past 3 months;(12)Being pregnant or in lactation.

#### 2.3.3 Eligibility criteria for healthy participants

##### 2.3.3.1 Inclusion criteria

Participants who meet the following criteria will be included as normal control:

(1)Age between 40 and 80 years (no gender restrictions);(2)Not in sub-healthy state according to the “Clinical Guidelines of Chinese Medicine on Sub-health” of China Association of Chinese Medicine (43);(3)No diagnosis of respiratory system diseases, digestive system diseases, and other conditions or states of obvious clinical significance within 1 year prior to enrollment;(4)Volunteering to cooperate with the study and sign an informed consent form.

##### 2.3.3.2 Exclusion criteria inclusion criteria

Participants who meet any of the following criteria will be excluded from the normal control group:

(1)Regular application of probiotics, prebiotics, or antibiotics;(2)Having gastrointestinal symptoms in the last week;(3)Being pregnant or in lactation;(4)Being in other clinical trials.

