### 2.10 Statistical analysis

Analyses of effectiveness, indicators of DNA library of gut microbiota, content of metabolites, percentage of immune cell and expression levels of inflammatory cytokines will be performed according to the Per Protocol Set (PPS) principle. The missing data will be filled in by multiple interpolation. SPSS 27.0 software (IBM Corp, New York) will be applied for statistical analysis. Quantitative indicators will be described by mean value (± standard deviation) or median (± interquartile range), and classification indicators by frequency and percentage. Baseline data will be analyzed using Chi-square or Fisher precision tests (data with frequency less than 5) and ANOVA. Sensitivity analyses will be performed using ANOVA.

The outcome of effectiveness, indicators of DNA library of gut microbiota, content of metabolites, percentage of immune cell and expression levels of inflammatory cytokines will be analyzed by linear mixed effects model. Fixed effects will be set for analyzing groups, COPD subtypes and smoking index (calculation method: smoking years × daily smoking number ÷20); Random effects for sub-centers and baseline outcome measures, both including intercept; Model-based covariance will be applied to test the fixed effects and coefficients, the degree of freedom will use residual method, and the maximum number of iterations will be set to 100. To control for type I error rates under multiple comparisons, the Benjamini–Hochberg method will be utilized for multiple comparison correction. Multiple linear regression will be used to analyze the relationship between clinical efficacy and gut microbiota, metabolites, immune cells and inflammatory factors. Statistical tests will be bilateral with *P* < 0.05 considered statistically significant.

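### The COPD versus healthy comparison is open to confounding because recent antibiotic and systemic steroid use excludes patients but not controls

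*Protocol article*

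**What the plan says.** For patients, section 2.3.2.2 lists "6)Application of antibiotics within the past 3 months;(7)Application of systemic glucocorticoids within the past 1 month" among the exclusions. Table 2 repeats both criteria.

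For healthy controls, section 2.3.3.2 has four exclusions. The first two are "1)Regular application of probiotics, prebiotics, or antibiotics;(2)Having gastrointestinal symptoms in the last week" and the last two are "3)Being pregnant or in lactation;(4)Being in other clinical trials". Table 2 gives the same four. None sets a look-back period for antibiotics, and none mentions glucocorticoids.

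Section 2.3.3.1 adds a health requirement for controls: "No diagnosis of respiratory system diseases, digestive system diseases, and other conditions or states of obvious clinical significance within 1 year prior to enrollment". It also requires that they are not in a sub-healthy state and sets the same 40 to 80 age range as for patients, with no restriction by sex.

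The comparison itself is planned. The abstract (Methods) says "Differences between COPD patients and healthy participants will be observed", and the Discussion says that comparison with the volunteers will establish the patients' pathological characteristics in microbiota, metabolism and immune inflammation. Controls give samples once (section 2.6.2.2). Section 2.10 describes a linear mixed model: "Fixed effects will be set for analyzing groups, COPD subtypes and smoking index", with sub-center and the baseline outcome as random effects.

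**The concern.** The 36 volunteers are the reference for deciding which microbes, metabolites and immune markers are abnormal in COPD. In a gut-microbiota study, a 3-month antibiotic exclusion for patients implies that recent antibiotics are thought to distort the measurement. The reference group is not held to that rule. Taken as written, a volunteer who recently finished a single antibiotic course, or recently took a systemic steroid, is not excluded on that ground, whereas a patient would be.

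Recent exposure can then differ systematically between the groups for a reason unrelated to COPD. That could create a difference or hide one. Because the difference is built into eligibility, it is best corrected before controls are sampled.

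**Working it through.** **Step 1. The two eligibility lists side by side**

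| Item | COPD patients (2.3.2.2, Table 2) | Healthy controls (2.3.3.1, 2.3.3.2, Table 2) |
|---|---|---|
| Antibiotics | Any use in past 3 months | Regular use only, no window |
| Systemic glucocorticoids | Any use in past 1 month | Not mentioned |
| Probiotics, prebiotics | Long-term use | Regular use |
| Gastrointestinal | Severe gastrointestinal or gut microbiota disorders | Symptoms in last week; no digestive disease diagnosed in 1 year |
| General health | Listed severe diseases | No clinically significant condition in 1 year; not sub-healthy |

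The probiotic rules are similar. The antibiotic and steroid rules are not. The section text and Table 2 agree on both lists, so the mismatch is a stated rule and not a slip in one place. The controls' health criteria concern diagnoses, states and symptoms. None addresses drug use as such.

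**Step 2. The plan's own figures**

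The dropout step in section 2.4.1 reproduces: 32 / (1 − 0.10) = 35.6, rounded up to 36 per group. That figure concerns the CAT outcome and has no bearing on this point. No separate calculation is given for the 36 controls, so there is no planned precision for this contrast to check against.

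**Step 3. What a given bias would do (illustration only)**

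Inputs from the document: 72 patients, 36 controls, two-sided 5% level. Assumed: a marker scaled to SD 1, a normal approximation, and no true difference.

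- SE of the group difference = √(1/72 + 1/36) = 0.204 SD.
- With bias b, the rejection probability is 1 − Φ(1.96 − b/SE) + Φ(−1.96 − b/SE).

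| Bias b (SD) | b/SE | False-positive rate, one feature |
|---|---|---|
| 0 | 0 | 5% |
| 0.05 | 0.24 | 5.7% |
| 0.10 | 0.49 | 7.8% |
| 0.15 | 0.73 | 11.4% |
| 0.20 | 0.98 | 16.5% |
| 0.30 | 1.47 | 31.2% |

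**Step 4. What would produce such a bias**

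If a fraction f of controls is recently exposed and exposure shifts the marker by s SD, then b = f × s. Both values are assumed:

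- f = 10%, s = 0.5: b = 0.05
- f = 10%, s = 1.0, or f = 20%, s = 0.5: b = 0.10
- f = 30%, s = 0.5: b = 0.15
- f = 20%, s = 1.0: b = 0.20
- f = 30%, s = 1.0: b = 0.30

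Fractions of 10% to 30% correspond to about 4 to 11 of the 36 controls. An unadjusted age gap acts in the same way: a gap of 0.5 to 1.0 SD with an age-marker correlation of 0.1 to 0.3 gives b from 0.05 to 0.30. The document supplies none of these values.

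**The case against.** The strongest reply is that the controls' health criteria already do most of the work. An infection that needed antibiotics, or a condition that needed systemic steroids, may well count as clinically significant within the year, and a volunteer with gastrointestinal symptoms in the last week is excluded. Table 1 also schedules medication history and demographics for healthy participants, so exposure and imbalance could be seen and handled in the analysis. This narrows the gap but does not close it. A short course for a minor complaint need not breach any stated criterion, and recording an exposure is not the same as excluding it.

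A reader might also infer that the section 2.10 model cannot be fitted to this contrast, because healthy people have no COPD subtype. If the model did include controls, subtype would be aliased with group: with an assumed three subtype indicators, all zero in controls, the design has 6 columns and rank 5. But section 2.10 does not assign that model to the healthy contrast. Its terms suit the acupuncture versus sham comparison, and ANOVA is named for baseline data. An undefined subtype would in any case be a problem of estimability, not a source of confounding.

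A third inference is that controls are unmatched. The article states no matching, but it condenses a fuller protocol, and silence there is not evidence that matching is absent.

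The planned Benjamini–Hochberg correction is no answer to the remaining gap: it needs p-values that are valid under the null, and bias removes that validity.

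**Conclusion.** The point holds in a limited form. The stated eligibility rules allow recent antibiotic and systemic steroid exposure to differ between patients and controls, so the cross-sectional comparison is open to confounding. It would go too far to say that the comparison is confounded: how many controls would be exposed, and which way any marker would move, cannot be derived from the document.

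The range of about 8% to 31% false positives per feature is conditional on an assumed bias of 0.1 to 0.3 SD. Its upper end needs, for example, about 11 of 36 controls exposed and a shift of a full SD. At 10% exposed and a 0.5 SD shift the rate is 5.7%, barely above nominal.

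The issue touches only the non-randomised comparison with volunteers. The randomised acupuncture versus sham contrast and the CAT primary outcome are unaffected. The change is still worth making because the reference group has no other stated purpose and the remedy is cheap.

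**What to change.** 1. Add to the healthy-control exclusions in section 2.3.3.2 and Table 2 the two look-back windows already used for patients: no antibiotics in the past 3 months and no systemic glucocorticoids in the past month.
2. State that the COPD versus healthy contrast is a baseline, cross-sectional analysis adjusted for age and sex, which the demographic data scheduled in Table 1 should provide, and for smoking index if it is recorded in controls. Table 1 does not name smoking, so this needs confirming.
3. Leave COPD subtype and the baseline-outcome term out of that analysis. Controls have no subtype, and their only sample is the baseline one.

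If controls have already been enrolled, use the scheduled medication history to repeat the analysis without those who fall inside the windows, provided it covers the relevant period.

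The cost is two eligibility lines, a sentence on the model and slightly slower recruitment of volunteers. The sample size does not change.
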